### Patient Enrollment and Randomization

Cardiac surgical patients will be recruited from the Frankel Cardiovascular Center (FCVC) at Michigan Medicine. Opioid-naive patients undergoing first-time, elective cardiac surgery through a full median or miniature sternotomy beginning September 3, 2019, were screened for a targeted enrollment of 154 patients for randomization. Approximately 600 to 750 patients meeting these criteria underwent surgery at Michigan Medicine in 2017. Opioid-naive is defined as opioid-free at the time of preoperative clinic history and physical examination.

Patients lost to follow-up will be censored for data analysis, and missing individual intervention points will be dealt with by multiple imputations, as appropriate. We will compare the clinical and sociodemographic attributes of patients who decline participation and patients lost to follow-up with those of patients with complete follow-up to assess potential responder bias. We estimated a 20% rate of missingness, which was incorporated into our power calculation. On the basis of historical institutional data, we anticipated approaching 5 to 10 patients per week for potential enrollment, with an approximate 5 to 7 month enrollment period within a 12-month study period for completion of clinical follow-up, data analysis, and manuscript production. Although this timeline was affected by the COVID-19 pandemic forcing a pause in enrollment between March 14th and the time of writing, we were 93.5% (144/154) enrolled at the time of pausing and remained optimistic about completing enrollment within our 12-month study period. We used block randomization with randomly variable block sizes generated with Stata 15 software (StataCorp LLC, College Station, TX) and computer randomization occurred with the treatment assignment tool (Treatment Assignment Tool-University of Michigan [TATUM]) from the Michigan Institute for Clinical and Health Research.

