##### Analytic Approach

Mean total GAD-7 and PHQ-9 scores at each of the 4 time-points (Table 1) will be compared between the 2 groups with two-tailed *t* tests, whereas categorical findings (eg, mild, moderate, or severe anxiety on the GAD-7 and minimal, mild, moderate, moderately severe, or severe depression on the PHQ-9) will be compared between groups using chi-square tests. In addition, repeated measures ANOVA (analysis of variance) tests will be performed for the GAD-7 and PHQ-9 across the 4 time-points to examine differences between groups while accounting for correlation over time within each patient. IES-R mean total scores will be compared between groups using a two-tailed *t* test, and the proportion of patients in each group meeting established cutoffs (≥24, ≥33, and ≥37) [64-66] will be compared with chi-square or Fisher exact tests, as appropriate. Chi-square tests will be used for the Picker Patient Experience Questionnaire to determine differences in mean proportions of *problems* reported out of the 15 items in the survey. The mean intrapatient difference between preoperative clinic and 30-day follow-up in functional status scores on the KCCQ-12 will be evaluated (≥5 point difference indicates a clinically important difference) and compared between study cohorts. Pain severity and pain interference scores will be determined (both out of 10) from the Brief Pain Inventory and generated for each patient. These 2 mean scores will be compared between groups using a two-tailed *t* test. Finally, pain score proportions on a 4-point scale (none, minimal, moderate, or severe) recorded through the 30-day postoperative questionnaire will be compared across groups using the chi-square test.

**Table 1 table1:** Schedule of survey instrument administration. The survey administration schedule is indicated for both study cohorts (ie, all patients).

Preoperative clinic visit for History and Physical	Day of discharge	30-day postoperative clinic visit	90-day postoperative clinic visit or phone call
GAD-7^a^	GAD-7	GAD-7	GAD-7
PHQ-9^b^	PHQ-9	PHQ-9	PHQ-9
KCCQ-12^c^	BPI^d^	Picker Patient^e^	N/A^f^
N/A	N/A	IES-R^g^	N/A
N/A	N/A	OPIOID^h^	N/A
N/A	N/A	KCCQ-12	N/A

^a^GAD-7: Generalized Anxiety Disorder 7-item scale.

^b^PHQ-9: Patient Health Questionnaire-9.

^c^KCCQ-12: Kansas City Cardiomyopathy Questionnaire 12-item short-form.

^d^BPI: Brief Pain Inventory.

^e^Picker Patient: Picker Patient Experience Questionnaire.

^f^N/A: not applicable.

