##### Power Analysis

Our primary endpoint is composite of health care utilization, defined as the total number of days spent at home within the first 30 days after surgery. Secondary endpoints include mean GAD-7 and PHQ-9, KCCQ-12, Picker Patient Experience Questionnaire, IES-R, and Brief Pain Inventory Scores and mean inpatient and outpatient opioid use.

We will compare mean days with a two-tailed *t* test and set the power of this study at 80% with alpha (Type I error) of .05 and the Cohen *d* effect size (defined as the difference in means divided by standard deviation) between medium (0.5) and large (0.8) [69,70], which yields a minimum sample size of 52 patients to detect a large effect size and 128 to detect a medium effect size [71]. Incorporating 20% missingness, a sample size of 154 patients will adequately detect a medium effect size. We next verified this statistically derived sample size with clinically relevant examples. Although most large series reporting opioid use report the median and interquartile range of OME [47,72], our sample size should be sufficient to satisfy the central limit theorem and use mean values. At our institution, the mean opioid use after sternotomy in 2017 was 200 OMEs. We estimated that to detect a 30% reduction in opioid use (mean 140 OMEs) with a standard deviation of 125 OME in the control and 100 OME in the intervention arms, a sample size of 114 would be required. For composite health care utilization, demonstrating a 3-day difference between the arms with a 6-day standard deviation would detect by a total sample size of 128 patients. With 154 patients, we should have adequate power to detect a difference in our primary outcomes for aims 1 and 2.

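### The chi-square test planned for the Picker questionnaire does not match the per-patient quantity it is meant to compare, and the unit of analysis is undefined

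*Protocol article*

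**What the plan says.** In the protocol article, Methods, Aim 1, Analytic Approach, the Picker sentence reads: "Chi-square tests will be used for the Picker Patient Experience Questionnaire to determine differences in mean proportions of". What is averaged is the share of the questionnaire's 15 items that a patient marks as a problem. No unit of analysis is named, and nothing is said about answers from the same patient being related.

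The Power Analysis section places the instrument among outcomes expressed as mean scores: "Secondary endpoints include mean GAD-7 and PHQ-9, KCCQ-12, Picker Patient Experience Questionnaire, IES-R, and Brief Pain Inventory Scores".

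The same Aim 1 paragraph treats the other mean scores differently. GAD-7, PHQ-9, IES-R and Brief Pain Inventory means are compared with two-tailed t tests, and repeated GAD-7 and PHQ-9 scores are analysed "while accounting for correlation over time within each patient".

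**The concern.** The named test and the named quantity do not fit together. Each patient contributes one proportion between 0 and 1, and the arms differ or not in the mean of those proportions. A chi-square test needs a table of counts from independent units. To run one here, the analyst must first decide what is being counted, and the article does not say.

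The choice matters because each way of building the table gives a different error rate or tests something else. Picker is the instrument that the article assigns to patient experience, and Aim 1 hypothesises a better hospital experience with the coach. A result on that question should not depend on an unstated choice of table.

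**Working it through.** **Inputs**

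- Items per patient: 15 (Aim 1, Analytic Approach).
- Alpha: 0.05. The Power Analysis section says "set the power of this study at 80% with alpha (Type I error) of .05" for the primary t test; I assume the same level for Picker.
- Patients: 154 in total (Power Analysis), with 20% missing ("We estimated a 20% rate of missingness", Patient Enrollment and Randomization). 154 × 0.8 = 123, or about 61 per arm if allocation is 1:1 (assumed). I also used 77 per arm, with no missing data.
- Intraclass correlation (ICC) of the 15 answers within a patient: not stated; assumed 0 to 0.30.
- Proportion of items reported as problems: not stated; assumed 0.1, 0.2 and 0.3, the same for all items.

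The article gives no Picker-specific figure to reproduce. Its general sample sizes, 128 for d = 0.5 and 52 for d = 0.8, do reproduce with a two-sample t test at 80% power.

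**Reading 1: all answers pooled** (15 × 61 = 915 per arm). The variance of the arm difference is larger than the chi-square assumes by the design effect DE = 1 + 14 × ICC. The true two-sided type I error is 2 × (1 − Φ(1.96/√DE)). The problem rate and the number of patients cancel out.

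| Assumed ICC | DE | 1.96/√DE | True type I error | Multiple of 5% | Simulated range |
|---|---|---|---|---|---|
| 0 | 1.00 | 1.96 | 0.050 | 1.0 | 0.047–0.052 |
| 0.02 | 1.28 | 1.73 | 0.083 | 1.7 | not run |
| 0.05 | 1.70 | 1.50 | 0.133 | 2.7 | 0.126–0.134 |
| 0.10 | 2.40 | 1.27 | 0.206 | 4.1 | 0.203–0.210 |
| 0.20 | 3.80 | 1.01 | 0.315 | 6.3 | 0.310–0.323 |
| 0.30 | 5.20 | 0.86 | 0.390 | 7.8 | 0.388–0.394 |

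The simulation is beta-binomial, with 8,000 runs per setting, over both arm sizes and all three problem rates.

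**Reading 2: one chi-square per item.** Each test uses independent patients and holds its level (simulated 0.050 to 0.052). With 15 tests and no adjustment, the chance of at least one false positive is 1 − 0.95^15 = 0.537 if items are independent. In simulation (4,000 runs, problem rate 0.2, 61 per arm) it was 0.544, 0.528, 0.496 and 0.467 for ICC 0, 0.10, 0.20 and 0.30. This reading also does not test a mean proportion.

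**Reading 3: the mean proportion with patients as denominator.** The test assumes variance p(1 − p)/n per arm, while the true variance is p(1 − p)(1 + 14 × ICC)/(15n). The ratio of true to assumed variance at ICC 0.30 is 5.2/15 = 0.347, so the type I error is 2 × (1 − Φ(1.96/√0.347)) ≈ 0.001. It is smaller at lower ICC. The simulations gave 0.000 to 0.001, so the test would almost never reject under the null.

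**Reading 4: any problem versus none.** Simulated type I error was 0.057 or below, but this is a different quantity from the one stated.

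**Comparator: t test on each patient's own proportion.** Simulated type I error was 0.045 to 0.053 across ICC 0 to 0.30, both arm sizes and all three problem rates.

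**The case against.** The strongest reply is that the article never says answers are pooled. A reader might infer that the plan treats one patient's 15 answers as independent and so inflates the false-positive rate several-fold. The text does not support that as a statement of fact. The unit is left open, and the plural in both tests and proportions is compatible with item-by-item testing, which has no clustering inflation. The size also depends on an ICC that the article does not give: it is 1.7-fold at 0.02 and absent at 0. This stands, and the pooled figures are therefore conditional.

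A reader might also infer that a false claim of better experience becomes likely. It does not follow. The 13% to 39% is two-sided, so false results in favour of the coach are about half of that, roughly 7% to 20%, against a nominal 2.5%.

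Nor should the criticism be extended to the chi-square tests on ordered categories, such as the 30-day pain scale. A chi-square there is a valid test that ignores order, and GAD-7 and PHQ-9 totals are also compared by t tests and repeated measures ANOVA.

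Finally, a full protocol or analysis plan that is not shown might name the unit. That would settle the ambiguity but not the mismatch: the article commits to a specific test for a specific quantity, and none of the four readings gives that quantity a correct error rate, unless answers within a patient are uncorrelated.

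**Conclusion.** Wrong as written, with limited reach. A chi-square test is not a test of a difference in mean per-patient proportions, and the article does not define what would be counted. Under pooling, the true error of a nominal 5% test is about 13% to 39% for an assumed ICC of 0.05 to 0.30, 8% at 0.02 and 5% at 0. Item-by-item testing gives about a 50% chance of at least one false positive over 15 items. Using patients as the denominator gives an error near zero.

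These figures assume a common correlation among the 15 answers, one problem rate for all items and 1:1 allocation. Some positive correlation is the natural expectation when one patient answers 15 questions about one hospital stay, but its size is unknown here.

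Picker is one of several secondary endpoints. The primary endpoint, its t test and its sample size are unaffected. The point should be corrected before analysis but does not threaten the trial's main conclusion.

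**What to change.** State the patient as the unit of analysis. Compute each patient's proportion (or count) of problems out of 15 and compare arms with a two-sample t test, which matches how the other mean scores are handled, or with a Wilcoxon test. A model of the item answers clustered by patient, such as GEE, is an acceptable alternative. If item-level results are also wanted, label them as descriptive or adjust for the 15 comparisons.

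The cost is a change to the analysis wording. No new data, patients or visits are needed.

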#### Aim 1: Assess the Effect of a Comfort Coach on Patient Experience

To address this aim, we will examine the effect of the comfort coach on perioperative anxiety, self-reported pain, functional status, and patient satisfaction. We will use the Generalized Anxiety Disorder 7-item scale (GAD-7) [56] anxiety assessment and Patient Health Questionnaire-9 (PHQ-9) [57] depression scale at 4 points: preoperative clinic visit, discharge, and at 30- and 90-day follow-up. The Kansas City Cardiomyopathy Questionnaire short-form (KCCQ-12) [58,59] will be administered at the preoperative clinic visit and 30-day follow-up to evaluate functional status. The Impact of Events Scale-Revised (IES-R) [60] will measure event-related psychological stress at 30-day follow-up, and the Picker Patient Experience Questionnaire [61] will be administered at the 30-day follow-up. The Brief Pain Inventory [62,63] will be administered at discharge to assess in-hospital pain. We hypothesize that patients who receive a comfort coach report a better hospital experience, improved functional recovery, and lower levels of depression, anxiety, stress, and pain.

##### Outcome Measures for Aim 1

Outcome measures for aim 1 exclusively consist of validated measures for anxiety, depression, stress, pain, and patient satisfaction (Textbox 1). These validated tools were adapted to better evaluate differences in pharmacological and nonpharmacological treatments and their corresponding effects and are included in the Multimedia Appendix 1.

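### KCCQ-12 is compared between arms as a pre-post change with no baseline covariate stated: unbiased, but less precise than baseline adjustment, and the 5-point remark follows the within-patient change

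*Protocol article*

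**What the plan says.** The KCCQ-12 is measured twice. Under Aim 1 of the Protocol article, it "will be administered at the preoperative clinic visit and 30-day follow-up to evaluate functional status". The Analytic Approach section for Aim 1 then fixes the quantity to be analysed: "The mean intrapatient difference between preoperative clinic and 30-day follow-up in functional status scores on the KCCQ-12 will be evaluated". A bracketed remark follows, and the sentence ends with the comparison of arms: "≥5 point difference indicates a clinically important difference) and compared between study cohorts". It names neither a test nor a baseline covariate for this instrument, and it gives no separate benchmark for the difference between arms.

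The KCCQ-12 is a secondary endpoint. The Power Analysis section says "Secondary endpoints include mean GAD-7 and PHQ-9, KCCQ-12" and continues with further instruments. The trial was sized on days at home, not on this score.

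**The concern.** Two things stand out.

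- **Precision.** Subtracting the baseline score in full is efficient only when the regression slope of the 30-day score on baseline is close to 1. Otherwise the subtraction adds noise that a baseline covariate would remove. Both scores are already collected, so the lost precision buys nothing.
- **Reading of the 5 points.** Every participant has a sternotomy operation between the two measurements. The change from clinic to day 30 therefore holds surgery, recovery and any coach effect together, in both arms. The bracket comes directly after that change. Only the difference between arms isolates the coach.

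At stake is the hypothesis of better functional recovery with a coach, for which the KCCQ-12 is the functional-status instrument.

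**Working it through.** **Inputs from the article**
- Analysed quantity: change from preoperative clinic to 30 days, compared between arms (Aim 1, Analytic Approach).
- Sizing test: "We will compare mean days with a two-tailed *t* test"; the plan also says it will "set the power of this study at 80% with alpha (Type I error) of .05" (Power Analysis).
- Stated sample sizes: the calculation "yields a minimum sample size of 52 patients to detect a large effect size and 128 to detect a medium effect size".
- Final size: "Incorporating 20% missingness, a sample size of 154 patients will adequately detect a medium effect size".

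**Inputs assumed**
- KCCQ-12 SD of 20, pre-post correlation rho from 0.2 to 0.8, and an arm difference of 10 points. None of these is in the article.
- Equal allocation; no ratio is stated. Then 154 × 0.8 = 123.2 evaluable, or 61.6 per arm, taken as 62.

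**1. The plan's own figures.** A two-sample t test (noncentral t, two-sided 0.05, 80% power) needs 63.8 per arm at d = 0.5, rounded up to 64, so 128 in total. At d = 0.8 it needs 25.5, rounded up to 26, so 52. Both stated figures reproduce. There is no stated KCCQ-12 figure to check.

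**2. Variances with equal SDs**
- Change score: Var = 2(1 − rho) × SD²
- Baseline-adjusted: Var = (1 − rho²) × SD²
- Ratio, adjusted to change: (1 − rho²) / [2(1 − rho)] = (1 + rho)/2
- 30-day score alone: Var = SD². The change score is noisier than this when 2(1 − rho) > 1, that is, when rho is below 0.5.

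**3. Numbers put in.** At rho 0.3, the change SD is 20 × √1.4 = 23.7 and the adjusted SD is 20 × √0.91 = 19.1. Power of a two-sided t test with 62 per arm for a 10-point difference:

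| rho | variance ratio | change | 30-day alone | adjusted |
|---|---|---|---|---|
| 0.2 | 0.60 | 59% | 79% | 80% |
| 0.3 | 0.65 | 65% | 79% | 83% |
| 0.5 | 0.75 | 79% | 79% | 89% |
| 0.6 | 0.80 | 87% | 79% | 93% |
| 0.7 | 0.85 | 95% | 79% | 97% |
| 0.8 | 0.90 | 99.2% | 79% | 99.6% |

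For a 5-point difference under the same assumptions, power is 21% against 30% at rho 0.3, and 34% against 41% at rho 0.6.

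**4. Unequal SDs.** Let k = SD after / SD before. The ratio becomes k²(1 − rho²) / (k² + 1 − 2·rho·k). Denominator minus numerator is (1 − rho·k)², which is never negative. So the adjusted analysis is never the noisier one, apart from one degree of freedom, and the two are equal when rho·k = 1. Two ends of a plausible grid:
- k = 0.7, rho = 0.3: 0.446 / 1.070 = 0.42
- k = 1.5, rho = 0.7: 1.1475 / 1.1500 = 0.998

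**5. The 5 points.** Suppose the coach has no effect and the SD of change is 20 (assumed). If surgery shifts both arms by +10, the share at or above +5 is 1 − Φ((5 − 10)/20) = 60% in each arm. If it shifts both by −10, the share is 1 − Φ((5 + 10)/20) = 23% in each arm. How many patients reach 5 points therefore depends on the course after surgery and says nothing on its own about the coach.

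**6. Validity of the comparison.** A shift common to both arms cancels in the difference. In 20,000 simulated trials with 62 per arm, rho 0.5, a common +10 shift and no coach effect, the t test on change rejected in 5.0%.

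**The case against.** The strongest reply is that nothing here is invalid. The comparison of arms is already planned in the same sentence, randomisation makes it unbiased, and step 6 shows the nominal error rate is kept. That stands in full.

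A reader might infer that surgery could trigger a 5-point success rule, or that each arm will get its own verdict, so that mean changes of +6 and +4 would count as important in one arm only. The article does not support this. The 5 points are an interpretive remark. No responder endpoint, proportion test or success criterion is built on them. Where cutoffs are to be tested, as for the IES-R in the same section, the article says so and names the test.

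It can also be said that the lack of a covariate is only inferred, since a condensed article names no model here and an analysis plan not shown might add baseline. A comparison of change with baseline as covariate would give the same arm estimate as the analysis proposed below. That limits how firmly the analysis can be called unadjusted. Still, the quantity to be compared is stated, and no adjustment is stated with it.

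Finally, the size rests on assumptions. The 10-point effect is twice the article's own benchmark, and a correlation below 0.5 has no support in the document. At a 5-point difference both analyses have low power for rho between 0.2 and 0.6. All of this stands. It bears on how much is gained, not on the direction.

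**Conclusion.** The point holds as a minor one on a secondary endpoint. As stated, the KCCQ-12 comparison is unbiased but gives up precision that baseline adjustment would recover at no cost in data. With equal SDs the adjusted variance is (1+rho)/2 of the change-score variance. Under the assumed SD, sample and 10-point difference, the gain in power is about 18 points at rho 0.3, 6 points at rho 0.6 and under half a point at rho 0.8. With unequal SDs it can be almost nil.

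The 5-point remark calls for clearer wording. A change of that size within an arm includes the effect of surgery and is not evidence for the coach. No flaw in the test and no wrong stated figure follows from it.

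**What to change.** - Compare the 30-day KCCQ-12 score between arms in a linear model with the preoperative KCCQ-12 score as covariate. Report the adjusted difference with its 95% confidence interval as the result.
- Keep the within-arm change as description only.
- State what the 5 points refer to. If they mean individual change, compare the proportion of responders between arms. If they mean the difference between arms, read the adjusted difference and its interval against them. The article does not settle which is meant, so the authors must say.

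The cost is a change of wording. Both scores are already in the survey schedule, and the model uses one further degree of freedom. The change should be made and dated before the data are analysed.

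### The ordered 4-point pain scale at 30 days is compared only by a general chi-square test, which ignores the order and costs about 17 points of power against a medium shift under assumed distributions

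*Protocol article*

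**What the plan says.** In the protocol article, the Analytic Approach under Aim 1 takes "pain score proportions on a 4-point scale (none, minimal, moderate, or severe") and says that these, "recorded through the 30-day postoperative questionnaire will be compared across groups using the chi-square test". No rank, trend or ordinal method is named for this item. The other pain measure, the Brief Pain Inventory, is given at discharge and covers in-hospital pain (Aim 1 text and Table 1).

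The same section applies chi-square to severity grades. For anxiety it gives as examples "mild, moderate, or severe anxiety on the GAD-7". For depression it names five grades and the test: "minimal, mild, moderate, moderately severe, or severe depression on the PHQ-9) will be compared between groups using chi-square tests". Those grades do not stand alone. "Mean total GAD-7 and PHQ-9 scores at each of the 4 time-points" are compared by two-tailed t tests, and repeated measures ANOVA "tests will be performed for the GAD-7 and PHQ-9 across the 4 time-points to examine differences between groups".

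The opening of Aim 1 hypothesises lower pain, anxiety and depression in the coached arm. The Power Analysis lists mean GAD-7, mean PHQ-9 and Brief Pain Inventory scores among the secondary endpoints. It does not list the 4-point pain item or the severity grades.

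**The concern.** Pearson's chi-square gives the same statistic if the four pain labels are shuffled. It asks whether the two distributions differ in any way, while the hypothesis asks whether pain moves down the scale. When the effect is a shift, nearly all the signal lies in one direction, yet the test is judged against a 3-degree-of-freedom critical value. The price is power.

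This matters most for 30-day pain because chi-square is the only comparison stated for it, and the item is the only pain score after discharge with a stated between-group test. The Discussion describes patients continuing techniques at home for 30 days, so a lasting effect on recovery pain would be looked for here. A real reduction could be reported as no difference.

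**Working it through.** **Inputs from the document.** "alpha (Type I error) of .05"; two-sided testing; total sample 154 with 20% missingness; a medium effect of d = 0.5 and a large effect of d = 0.8; four pain levels.

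**Inputs assumed.** 1:1 allocation (the ratio is not stated); the category distribution; the latent-normal form of the shift. The article's only anchor for the distribution is the figure of up to 81% with some pain at 1 month (Rationale for the Study).

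**The plan's own figures.** The noncentral t calculation for d = 0.5 and d = 0.8 at 80% power gives totals of 128 and 52, as the Power Analysis states. These concern a t test on days at home. The article gives no power for any ordinal comparison.

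**Evaluable patients.** 154 × 0.8 = 123.2, or 61.6 per arm, taken as 62.

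**Cost of the extra degrees of freedom.** The noncentrality that gives 80% power on 1 df is 7.85. The same noncentrality gives 70.9% on 2 df, 64.5% on 3 df and 59.5% on 4 df. For a four-level scale this is a loss of about 15.5 points when all the signal is directional.

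**Worked scenario for pain.** Control: 15/40/35/10%. Shifting the latent normal by 0.5 SD toward less pain gives about 29.6/43.8/22.8/3.7% in the intervention arm.

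- *Chi-square.* Noncentrality = n × Σ (p − q)²/(p + q) = 62 × (0.0478 + 0.0017 + 0.0258 + 0.0290) = 62 × 0.1043 ≈ 6.5 (6.42 without rounding). Against the 3-df critical value of 7.81, power is about 55%.
- *Wilcoxon.* P(intervention lower) + ½P(tie) = 0.4715 + 0.1516 = 0.623. With tie correction 1 − Σ(pooled proportion)³ = 0.891, SE = √(0.891 × 125 / (12 × 62²)) = 0.0491. So z = 0.123/0.0491 = 2.50, and approximate power is Φ(2.50 − 1.96) ≈ 71%.

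Since 2.50² ≈ 6.3, almost all of the 6.42 sits on one degree of freedom.

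**Simulation, 62 per arm, control 15/40/35/10%.**

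| Latent shift | Chi-square | Wilcoxon | Loss |
|---|---|---|---|
| 0 | 5% | 5% | none |
| 0.3 SD | 22% | 34% | about 12 to 13 points |
| 0.5 SD | 55% | 72% | about 17 points |
| 0.8 SD | 94% | 98% | about 4 points |

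A control distribution of 25/35/30/10% again gives about 55% against 72% at 0.5 SD. With 19% reporting no pain (the 81% anchor) and 64 per arm, the result is 56% against 73%. With 61 to 77 per arm and several distributions, the loss at 0.5 SD stays at about 15 to 18 points.

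**Grades, for comparison, at 0.5 SD.** The loss is about 9 to 11 points for the three GAD-7 grades named, 17 to 18 if a fourth grade below mild is added, and 20 to 24 for the five PHQ-9 grades.

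**The case against.** The strongest reply is that little rests on this test. The 4-point item is not a listed secondary endpoint; the listed pain endpoint is the Brief Pain Inventory, which has a t test. Chi-square is valid here, and the percentages by arm would show the direction of any difference. All of that stands. It makes the change a cheap improvement and not a repair of a central analysis. It does not supply another test for pain at 30 days.

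Three stronger readings are tempting, and the document does not support them.

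- *That all three ordered scales lose 17 to 24 points.* That range needs a medium shift, assumed distributions and four or five categories. The three GAD-7 grades named give about 10.
- *That the anxiety and depression hypotheses are left without a suitable test.* They are tested on total scores by t test and repeated measures ANOVA, and the means are the listed endpoints. The graded comparisons are supplementary.
- *That sparse upper categories invalidate the chi-square.* Expected counts below 5 are likely in the top categories, but simulated type I error stayed between 4.3% and 5.2%, so no inflation is shown. A Fisher fallback for each table is detail that an article commonly leaves to the full plan.

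**Conclusion.** The point holds for the 30-day pain scale. The article fixes an order-blind test as the only stated comparison of an ordered outcome with a directional hypothesis. At the medium effect used in the Power Analysis, the loss is about 17 points (55% against 72%) with 62 per arm. This size is conditional on a latent-normal shift and on category distributions that the document does not give, and it shrinks for smaller and larger effects.

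For the GAD-7 and PHQ-9 grades this is a matter of tidiness, since the trial's power on those scales does not depend on the graded tests. The primary endpoint, days at home, and its sample size are not touched.

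**What to change.** In the Aim 1 Analytic Approach, replace the chi-square for the 30-day pain scale with a tie-corrected Wilcoxon rank-sum test, or with proportional-odds regression reporting a common odds ratio and 95% CI. Choose one before the data are analysed, and keep the category percentages by arm as description. If the GAD-7 and PHQ-9 grades are tested at all, use the same ordinal method; leaving them descriptive is equally acceptable.

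The cost is one sentence and no new data. There are two downsides. An ordinal test is less sensitive to non-monotone differences, which the plan does not hypothesise. The regression option also adds a proportional-odds assumption that would need to be examined.
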